### Sample size

Sample size calculation followed Hemming et al. [7]’s study by fixing the number of clusters per arm to be 12 clusters, and then estimated the cluster size and total sample size. In the current study, it was assumed that the *i*-PUSH program could yield an effect size of 0.4 standard deviation in terms of health care utilization with an intracluster correlation (ICC) of *ρ* = 0.014. The estimates of the ICC were derived from Geng et al. [8]’s, study conducted in Nandi County which used high-frequency data on diaries on health-seeking behaviors and financial expenditures over 1 year (October 2012–October 2013). The calculation of the ICC was based on health care utilization measured as visits to any formal health provider, unconditional on reported health symptoms. It hypothesized a confidence interval of 95%, a margin-of-error of 5%, and a power of 80%. With a cluster size per arm of 12 clusters, and a total number of women per cluster of 10, the total sample size was 120 households per arm and 240 households for the full study.

To keep sample size at par, households that dropped out of the study before the start of the intervention were replaced with new eligible households on a rolling basis for a maximum period of six months, or until the program started.

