## Expected outcomes

Overall, the outcomes of interest for this evaluation study that are measured during the 18 months of follow-up include the following:

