### Primary outcomes (health care utilization and health expenditures)

Absolute number of visits to any formal health care provider for treatment of illness or injury (to measure curative healthcare utilization), over the full period between baseline and endline.

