### Baseline and endline survey instruments

The quantitative evaluation starts with a baseline survey before the rollout of the *i*-PUSH program and is completed by an endline survey conducted approximately 1 year after the *i*-PUSH introduction. Both surveys include modules on household demographics, socio-economic indicators, food and non-food consumption indicators, financial inclusion, participation in community networks, as well as self-assessed health status, health-related knowledge and behavior, health care utilization and health expenditures, maternal health, mental health, intra-household decision-making processes, and gender dynamics. In addition, the endline survey will include a satisfaction module on participation in the *i*-PUSH program for women in the treatment areas only and will be collected virtually using telephone interviews due to the COVID-19 pandemic. The household head or the most knowledgeable household member responds to the household roster, household-level modules including health care utilization and expenditures, and questions about under-aged household members. The focal person for the modules on maternal health, intra-household decision-making and health knowledge and behavior is the WRA in the household. All remaining individual-level modules (mental health, preferred clinic, mobile money use, savings groups and financial instruments) are reported by all adult individuals in the household (Table 2 in Appendix).

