with *Y*_*ij*_, *X*_*ij*0_ the posttest and pretest/baseline measures of the outcome for the *ith* respondent from the jth cluster, respectively. Treament_*ij*_ is a dummy for being assigned to the treatment group. It takes one if the respondent belongs to the intervention cluster and zero if control. *α*_2_ is the ITT effect or the impact of the *i*-PUSH program. We will use an OLS model with standard errors clustered at the level of the community units.

In addition to pretest measures, all other baseline covariates such as age, education, socioeconomic status (wealth quintile), crowding (persons per room), and occupation, will also be included in Equation (1). Thus, in Equation (1), the treatment effect of the *i*-PSUH program *α*_2_ assesses the treatment difference on post-treatment outcome adjusted for baseline.

We will assess whether the *i*-PUSH will significantly contribute in empowering women. For self-reported surveys on women empowerment, we will construct a total score of women’s empowerment which is based on a factor analysis of the various domains on which the woman indicates that she has sole, joint, or no decision-making power within the household (for each domain, the decision-making binary indicator will be equal to 1 if the woman respondent makes the decision alone or jointly with her partner and 0 otherwise). This total score will be used as the dependent variable, and Equation (1) will be used to estimate the impact of *i*-PUSH program on women’s empowerment. Furthermore, we will follow Almås et al. (2018) to construct an alternative measure of women’s empowerment based on the decision in the empowerment game. This dependent variable will be the willingness-to-pay which is the share that the woman is willing to pay in order to receive the amount herself in private rather than giving a (higher) amount to her husband. Interim data analyses (e.g., for policy briefs) are done using baseline and weekly diaries data to inform the context and implementation of the research or *i*-PUSH program.

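### The primary visit count starts at baseline, before i-PUSH is rolled out; the untreated weeks cost power, by an amount the article's conflicting timelines leave open

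*Protocol article*

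**What the plan says.** Under Primary outcomes, the article defines the outcome as the absolute number of visits to formal providers for illness or injury, counted "over the full period between baseline and endline". The passages that bear on timing are these:

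- Expected outcomes: outcomes are "measured during the 18 months of follow-up".
- Baseline and endline survey instruments: "The quantitative evaluation starts with a baseline survey before the rollout of the" programme, and there is "an endline survey conducted approximately 1 year after the" introduction of i-PUSH.
- Study design and randomization procedure: baseline data were used to pair the villages. The coin flip followed, and after it the training of community health volunteers, who then introduced the wallet and the insurance offer.
- Sample size: households lost before the intervention were replaced "for a maximum period of six months, or until the program started".
- Financial and health diaries: the diaries run from baseline to endline and record the date of each provider visit.
- Abstract, Methods: the weekly diaries are described as lasting one year.

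In Data management and analysis, the model is an OLS ANCOVA with a treatment dummy: "It takes one if the respondent belongs to the intervention cluster and zero if control". The outcome there is called the post-test measure. The same section also plans to pool all rounds, baseline and follow-up, into one panel.

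**The concern.** The counting window opens before the programme does. From baseline to roll-out the treatment villages receive nothing, so any difference between arms in those weeks is noise. Those visits nevertheless enter the primary count.

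What is at stake is mainly precision. There are 24 villages and 240 households, and the design only just reaches its 80% target, so it has little room for extra variance. A second risk is interpretation. If the result is reported per month, in SD units or per diary round, it averages treated and untreated time and understates what i-PUSH does once it is in place.

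A smaller matter points the same way. Replacement households join after baseline, so a count from baseline is not fully observed for them.

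**Working it through.** **Step 1. Reproduce the plan's sample size.** Inputs from Sample size: effect 0.4 SD, ICC 0.014, 12 villages per arm, 10 households per village, 80% power; two-sided 5% is taken from the 95% confidence level.

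- Individually randomised n per arm = 2 × ((1.96 + 0.84)/0.4)² = 98.1.
- With the number of clusters fixed, m = n(1 − ρ)/(k − nρ) = 98.1 × 0.986/(12 − 98.1 × 0.014) = 9.1, rounded up to 10. This gives the stated 120 per arm and 240 in total.
- Standard error of the difference in SD units = √[2 × (0.014 + 0.986/10)/12] = 0.137. Power at 0.4 SD is 83% (normal) or 80% (t, 22 df).

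**Step 2. Length of the lead-in.** The article implies two answers.

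- 18 months less about 12 months = about 6 months, which is 6/18 = 33% of the window.
- One-year diaries that span baseline to endline, with endline about a year after introduction, leave a lead-in near zero.

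It cannot be exactly zero, because pairing used baseline data. The six-month replacement limit is a ceiling, so it is compatible with 6 months but does not establish it. I therefore use 1, 3 and 6 months.

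**Step 3. Effect on the longer count.** Assume 0.4 SD applies to the 12-month count after roll-out and that the lead-in effect is zero. The added visits are the same, but the SD grows. For a window of T months, the ratio of its SD to the 12-month SD lies between √(T/12), if months are independent within a household, and T/12, if they are perfectly correlated. The article gives no such correlation, so both limits are shown, without baseline adjustment.

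| Lead-in | T (months) | Untreated share | Standardised effect | Power (normal) |
|---|---|---|---|---|
| 0 | 12 | 0% | 0.40 | 83% |
| 1 month | 13 | 8% | 0.38 to 0.37 | 80% to 77% |
| 3 months | 15 | 20% | 0.36 to 0.32 | 74% to 65% |
| 6 months | 18 | 33% | 0.33 to 0.27 | 66% to 50% |

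For example, at 6 months: 0.4/√1.5 = 0.327 and 0.4/1.5 = 0.267. With t on 22 df the 6-month range is 63% to 46%. Read the other way, 0.4 SD on an 18-month count needs 0.4 × √1.5 = 0.49 to 0.4 × 1.5 = 0.60 SD on the 12 months after roll-out.

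**Step 4. Which scale is diluted.** On the total count, the expected difference is (lead-in effect = 0) + (post-roll-out effect), so it is unchanged. Per month, the same difference is divided by 18 instead of 12, a reduction of 33%; with a 3-month lead-in the reduction is 3/15 = 20%.

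**Step 5. Baseline adjustment.** Suppose a one-month baseline count is the covariate and r is the correlation between monthly counts (both assumptions). With monthly variance 1, the variance of an M-month count given the covariate is M(1 + (M − 1)r) − (Mr)². Applying it to M = 12 and M = 18, with the same added visits, gives:

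| r | Power, 12 months after roll-out | Power, 18 months from baseline |
|---|---|---|
| 0 | 83% | 66% |
| 0.1 | 85% | 59% |
| 0.3 | 92% | 65% |
| 0.5 | 98% | 78% |
| 0.7 | over 99% | 94% |

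Adjustment raises power in both windows when months are correlated. It therefore removes the lower part of the unadjusted range at high r, but the 18-month window stays behind throughout.

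**The case against.** Four objections carry weight.

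1. *The six months is inferred.* This stands. No sentence gives the gap, the Abstract's description of the diaries points to a shorter one, and Table 1 (the schedule, not legible in the text available to me) may settle it. A reader might conclude that a third of the window is untreated; the article supports that only as the upper end.

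2. *The primary estimate is not biased.* This also stands. A reader might infer that the treatment coefficient is attenuated. With an absolute count and OLS, visits that carry no effect cancel in expectation, and the coefficient still estimates the visits added by i-PUSH. Attenuation arises only after rescaling to months, SD units or rounds.

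3. *The pooled model may already exclude lead-in rounds.* It is tempting to say that the treatment dummy equals one in untreated outcome rows. The article calls the dependent variable the post-test measure, which argues against this, while its plan to combine all rounds leaves it possible. It is an open reading, not a settled fault.

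4. *The 0.4 SD may have been meant for the whole window.* Sample size ties it to no period. If so, nominal power is unchanged, but the effect needed after roll-out is larger (0.49 to 0.60 SD with a 6-month lead-in).

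Intention-to-treat is no defence of the present window. It fixes the arm in which a household is analysed, not the date on which counting starts.

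**Conclusion.** The point holds as a loss of precision of uncertain size and an imprecisely chosen window. It does not make the primary analysis invalid. Some untreated time is certain, since pairing, randomisation and training all follow baseline. Its length, somewhere from short to about 6 months, cannot be fixed from the article, and the passages on duration need to be reconciled.

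The loss without adjustment runs from a few percentage points (1 month) to between 17 and 33 points (6 months: 83% less 66% or 50%). That rests on 0.4 SD applying to the year after roll-out and on a zero effect before it. The planned baseline adjustment recovers part of the loss, and the 50% figure in particular should not be quoted as expected power. Dilution by up to a third applies only to rescaled or per-round estimates, and to the pooled model only if lead-in rounds serve as outcome rows.

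This is a cheap improvement and should be made: should-fix, with moderate confidence on size.

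**What to change.** - Define the primary outcome as curative visits from the date i-PUSH starts in the pair's treatment village to endline, using the same calendar date for its control village. Tie the date to village roll-out, not to household enrolment, so that intention-to-treat is kept.
- In the pooled models, state that only diary rounds after that date are outcome rows.
- Use pre-roll-out diary visits as the baseline covariate where available.
- State the window to which the 0.4 SD applies.
- Reconcile the 18-month follow-up, the one-year diaries and the interval from introduction to endline, and give the lead-in explicitly.
- Report the baseline-to-endline count as a sensitivity analysis.

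The cost is wording in the outcome definition and analysis plan. No new data are needed, because the diaries already hold visit dates. The downsides are a shorter counting window and a small change to the stated primary outcome, which should be documented as such and made before outcomes are compared by arm.

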### Secondary outcomes

#### Health outcomes

Proportion of children under 5 who are fully immunized (to measure preventive healthcare utilization among young children).Proportion of pregnant women who complete their maternal care journey, i.e., 4 ANC visits, skilled birth attendant, 1 PNC visit (to measure maternal healthcare utilization among pregnant women).Proportion of children malnourished (anthropometrics) for children under 5.Proportion of children under 5 experiencing common childhood illnesses (diarrhea, acute febrile illnesses, acute respiratory infections) for children under 5.Out-of-pocket health expenditures.

#### Health knowledge and behavior

Knowledge on maternal and child health.Proportion of children under 5 sleeping under a bed net.

#### Women’s empowerment

Financial and health related decision-making power of women.

## Data collection instruments and techniques

Data collection consists of four main components: (1) a qualitative study, (2) baseline and endline household surveys, (3) weekly financial and health diaries interviews with all adults and emancipated minors in the households, and (4) behavioral lab-in-the-field experiments. Both quantitative and qualitative tools were piloted in Nairobi slums and debriefed to the research team including the field team.

### Qualitative study

The study uses qualitative data collection methods to get a deeper understanding of the perceptions and behaviors of the population on health insurance and health care utilization, to feed into the quantitative instrument design at baseline and to complement findings from the quantitative surveys at endline. This will help understand the motivations, drivers, and obstacles to savings for insurance in the target population. The qualitative baseline study is based on in-depth interviews (IDIs, *n* = 20) and focus group discussions (FGD, *n* = 4) with eligible men and women who were purposively sampled after CHVs’ mobilization to willingly participate in the study. Another qualitative study will be conducted parallel to the quantitative endline survey to provide additional under-the-skin description and/or for improved interpretation if the impact evaluation yields unexpected results.

### Baseline and endline survey instruments

The quantitative evaluation starts with a baseline survey before the rollout of the *i*-PUSH program and is completed by an endline survey conducted approximately 1 year after the *i*-PUSH introduction. Both surveys include modules on household demographics, socio-economic indicators, food and non-food consumption indicators, financial inclusion, participation in community networks, as well as self-assessed health status, health-related knowledge and behavior, health care utilization and health expenditures, maternal health, mental health, intra-household decision-making processes, and gender dynamics. In addition, the endline survey will include a satisfaction module on participation in the *i*-PUSH program for women in the treatment areas only and will be collected virtually using telephone interviews due to the COVID-19 pandemic. The household head or the most knowledgeable household member responds to the household roster, household-level modules including health care utilization and expenditures, and questions about under-aged household members. The focal person for the modules on maternal health, intra-household decision-making and health knowledge and behavior is the WRA in the household. All remaining individual-level modules (mental health, preferred clinic, mobile money use, savings groups and financial instruments) are reported by all adult individuals in the household (Table 2 in Appendix).

### Financial and health diaries

This study uses weekly financial and health diaries data collection methodology as its core research instrument, because this technique is well suited to address the research objectives by providing a granular insight into the financial lives and health-related decisions of participating households. The diaries are collected over the full study period between baseline and endline survey. The financial diaries record all financial transactions such as purchases, gifts, remittances, and loans, including those between household members in the 7 days prior to each interview. Transactions are described by type, incoming or outgoing cash, amount, purpose, transaction partner, and date. The health diaries provide a detailed picture of the incidence of illnesses and injuries, as well as preventive and curative health-seeking behavior. Health diaries collect data on all health events that occurred to any of the household members (respondents, their children and other household members) in the 7 days prior to each interview. This includes symptoms, whether any health care was sought, which health provider was visited, health services received, out-of-pocket health expenditures, date of onset of the symptoms, and date of provider visit(s).

Respondents to the weekly diaries interviews are all adults in the study households who are economically active (i.e., who handle money, excluding young adults who are still studying) and capable of conducting the interview (i.e., excluding very old-age or disabled household members). Emancipated minors, i.e., teenage girls who are a mother or who are pregnant, are also included as diaries respondent. The financial diaries are reported by each individual him- or herself. The health diaries can be reported by one individual for the entire household.

Data are collected through structured and formatted digital tools that allow to analyze data as they are recorded and improve data collection tools mid-course of the process. The short recall period drastically reduces recall bias and ensures that both major and minor illness episodes, including those with foregone care are reported. Because interviewers visit households weekly, they build a relationship of trust, which enables the diaries to capture also more sensitive health events. This is of particular importance in relation to capturing maternal and child health experiences.

Qualified fieldworkers were recruited and trained on data collection tools and techniques. Diaries data are collected through personal interviews in a conversation-like manner. Interviewers record information navigating through a specialized software program while the interview unfolds. The tool was administered face-to-face using tablets and took about 10–15 min. Prior experience of the research team with similar data collection indicates that such interviews generally last 10–15 min per household as both interviewers and respondents get more experienced. To reduce burden on the respondents, interviewers take care in planning the day, time, and location of the weekly interviews at the convenience of the respondent. The respondents are interviewed separately and in private spaces to ensure confidentiality. The COVID-19 situation has switched the mode of data collection to telephone interviews. Fieldworkers were retrained on telephone interview ethics and techniques. This will be implemented until the crisis recedes.

At regular intervals, the weekly diaries are complemented with pop-up modules. In particular, these include on a monthly basis, a pregnancy module, perinatal depression, and general mental health, and on a quarterly basis, food consumption of children, anthropometrics of children and their mothers. Since the COVID-19 outbreak, a monthly module has been added to assess the effect of COVID-19 pandemic on COVID19-related knowledge, preventive behavior (such as hand-washing and social distancing), mobility, barriers to health-seeking behavior, and fear/worries.

### Behavioral lab-in-the-field experiments

Diaries respondents are also invited to participate in a number of incentivized behavioral lab-in-the-field games to measure women’s empowerment (baseline, midline and endline) and risk attitudes (midline and endline only). As is standard in the behavioral economics literature, respondents can earn (small) amounts of money dependent on their decisions. This has been shown to improve accuracy of responses. The research team has extensive experience in conducting similar games in Kenya, Tanzania, Nigeria, and elsewhere. All payments are made directly to the respondent through M-PESA.

### Data management and analysis

Trained team leaders are situated in the field to supervise real time data collection. Data quality is ensured by regular spot checks and sit-ins to approximately 5–10% of each fieldworker’s daily work to verify authenticity of the data collected. Data collection is done electronically using tablets, with spot checks for quality control. The field supervisors certify the quality of the data through editing the data before they are transferred to the database. Once the data collection is completed and synchronized in a centrally located database, all inconsistencies are resolved prior to data analysis. Data quality is checked by a qualified data management team within the affiliated research organizations. An automated routine to check on data completeness, correctness, and consistency runs on 100% of the collected data. A discrepancy report is generated to help in following upon any inconsistencies, errors or missing data with the responsible interviewer. Similarly, the quality of qualitative data will be ensured through recruitment and training of qualified field interviewers with experience in qualitative data collection. A qualified transcriber will transcribe the interviews verbatim and double coding of about 10% of the transcripts will also be done to ensure consistency in the application of the codes. Access to data is granted for all research teams in respective research organizations. Data auditing is carried out by the research team on a progressive basis on weekly basis throughout the study duration.

The final analysis will investigate the extent of contamination (e.g., whether participants who were assigned to the control group nevertheless participated in the intervention) and appropriately account for it. The final will any risks of contamination, e.g., it will exclude those participants who are randomized to the intervention but do not adhere to the intervention.

Quantitative data will be analyzed using Stata version 14 statistical software. The first set of analysis will consist of descriptive statistics and will summarize and compare using measures of central tendency and dispersion (mean (SD), range and median). This will allow us to examine participants’ characteristics across the different sub-groups. We will first check whether the outcomes and covariates in the control group and treatment group are comparable at baseline using *t* test adjusted for clustering at the village unit for continuous variables and cluster-adjusted chi-square for binary variables. The second set of analysis will consist of assessing the causal effect of the *i*-PUSH intervention via an analysis of covariance (ANCOVA) based on intention-to-treat (ITT) analysis (all respondents who are randomized will be included in the statistical analysis and will be analyzed according to the group they were initially/originally assigned). To account for clustering of data at the village level, multi-level mixed models will be used. In addition, a generalized linear mixed model for repeated measures with random components will be used.

Based on our research questions, we will explore several additional econometric models. We will explore the impact of the *i*-PUSH program on health outcomes (healthcare utilization, health status, percentage of children who are fully immunized, etc.) and financial outcomes (percentage of women using NHIF/MTIBA to access services, percentage of people enrolled in NHIF through M-TIBA, percentage of people saving through M-TIBA, total amount saved on M-TIBA, etc.) via an analysis of covariance (ANCOVA) based on ITT analysis. Since we will have several rounds of data collection on the same respondents, we will combine all rounds of data collection (baseline and follow-up waves), and we will run an ANCOVA econometric model on a pooled panel data. More specifically, in the econometric model below, we will regress the follow-up measurement of the outcome variable (dependent variable) on the following covariates: baseline measurement (pretest measurement) and treatment group while controlling for the baseline socio-demographic characteristics such as maternal age, education, socioeconomic status (wealth quintile), crowding (persons per room), occupation, etc. The considered model is thus:
1$$ {Y}_{ij}={\alpha}_0+{\alpha}_1{X}_{ij0}+{\alpha}_2{\mathrm{Treament}}_{ij}+{e}_{ij t}, $$

with *Y*_*ij*_, *X*_*ij*0_ the posttest and pretest/baseline measures of the outcome for the *ith* respondent from the jth cluster, respectively. Treament_*ij*_ is a dummy for being assigned to the treatment group. It takes one if the respondent belongs to the intervention cluster and zero if control. *α*_2_ is the ITT effect or the impact of the *i*-PUSH program. We will use an OLS model with standard errors clustered at the level of the community units.

In addition to pretest measures, all other baseline covariates such as age, education, socioeconomic status (wealth quintile), crowding (persons per room), and occupation, will also be included in Equation (1). Thus, in Equation (1), the treatment effect of the *i*-PSUH program *α*_2_ assesses the treatment difference on post-treatment outcome adjusted for baseline.

We will assess whether the *i*-PUSH will significantly contribute in empowering women. For self-reported surveys on women empowerment, we will construct a total score of women’s empowerment which is based on a factor analysis of the various domains on which the woman indicates that she has sole, joint, or no decision-making power within the household (for each domain, the decision-making binary indicator will be equal to 1 if the woman respondent makes the decision alone or jointly with her partner and 0 otherwise). This total score will be used as the dependent variable, and Equation (1) will be used to estimate the impact of *i*-PUSH program on women’s empowerment. Furthermore, we will follow Almås et al. (2018) to construct an alternative measure of women’s empowerment based on the decision in the empowerment game. This dependent variable will be the willingness-to-pay which is the share that the woman is willing to pay in order to receive the amount herself in private rather than giving a (higher) amount to her husband. Interim data analyses (e.g., for policy briefs) are done using baseline and weekly diaries data to inform the context and implementation of the research or *i*-PUSH program.

